#### Variables influencing the effect of acute care nurse practitioner practice related to patient characteristics

Eleven influencing variables related to patient characteristics will be measured. For each patient, sociodemographic characteristics (e.g., sex, age) will be measured. The total length of stay at the hospital will be measured, which includes the stay in the ICU and postoperative cardiac surgery unit. The type of cardiac surgery will be collected from a categorical variable with three categories: 1) CABG, 2) valve repair, and 3) CABG/valve repairs. Comorbidities will be measured and operationalized from the Charlson Comorbidity Index (CCI) [44, 45]. A total score of 24 points will be calculated for each patient based on the 17 clinical conditions included in the CCI (S4 Appendix). The length of stay in the postoperative cardiac surgery unit will be collected for each patient. The hospital 30-days readmission at the postoperative cardiac surgery unit after discharge will be measured for each patient from a dichotomous variable.

Four influencing variables related to the patient characteristics in the ICU setting will be measured. The total number of hours hospitalized in the ICU will be measured from the time (in hours) of admission to the ICU after the surgery and the time (in hours) of discharge of the patient. The postoperative prolonged mechanical ventilation will be measured from a dichotomous variable. A prolonged mechanical ventilation will be confirmed if the time under mechanical ventilation exceeds 24 hours. The failed extubation of the patient and reintubation after first extubation will be measured with a dichotomous variable. The number of episodes of ICU readmission after initial discharge will be measured for each patient.

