Based on the International Council of Nurses guidelines, the NP is an advanced practice nursing role, based on a graduate or postgraduate education and an in-depth nursing and clinical expertise (e.g., prescription of the pharmacotherapy, diagnosis, etc.) [21–23]. In postoperative cardiac surgery, ACNP have been implemented in interprofessional teams and performed activities such as the clinical and psychosocial assessment of patients, the prescription and management of pharmacotherapy, laboratory tests and clinical interventions, lifestyle promotion, teaching of coping strategies, preparation for hospital discharge, and the management of consultations and external resources [24]. International research teams [23, 25] have examined the practice of ACNP within postoperative cardiac surgery settings. They identified significant associations between the ACNP’ practice and higher patient satisfaction during their hospital stay, higher rates of patients participating in cardiac rehabilitation programs, and reduced length of stay at the hospital after the cardiac surgery. In contrast, other research teams [21, 26] did not identify significant associations between ACNP practice and patient and organizational outcomes within postoperative cardiac surgery settings. More specifically, the authors suggested that the difficulty of recruiting participants, the high attrition rate, the small sample sizes, and the inability to adjust the data analysis for confounding variables related to the patient and interprofessional teams’ characteristics were important limits contributing to the non-significant findings [21, 26].

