### Study setting

This study will be conducted at a UHC in Québec, Canada, where approximately 1,000 cardiac surgeries are performed annually in a 36-bed postoperative cardiac surgery unit.

After cardiac surgery, patients are admitted to the intensive care unit (ICU), and are under the care of ICU teams. At the time of data collection, the ICU teams in Québec, Canada did not include ACNPs. On average, patients are hospitalized for 24 hours in the ICU before being transferred to the postoperative cardiac surgery unit. Patients readmitted to the ICU are under the care of ICU teams.

Upon admission to the postoperative cardiac surgery unit, patients are assigned to the care of interprofessional teams with or without ACNPs. Team assignment depends on the current workload of each team, and the availability of the beds in the unit. Interprofessional teams with ACNPs are responsible for 16 of the unit’s beds (44%) and interprofessional teams without ACNP are assigned 20 of the unit’s beds (56%). Patients are followed by their respective teams from their admission to the cardiac surgery unit until hospital discharge or death. On average, the length of stay at the hospital after the surgery ranges from 9 to 11 days [33].

Interprofessional teams with and without ACNPs include the following: cardiac surgeons and physician residents, nursing teams, skin and wound care specialists, physiotherapists, nutritionists, respiratory therapists, social workers, and other medical specialists. Interprofessional teams with and without ACNPs ensure daily follow-up of patients, assessment of the patient’s clinical and psychosocial condition, management of pharmacotherapy, clinical interventions, prescribing and monitoring of laboratory tests, lifestyle promotion, and the preparation of patients for hospital discharge.

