### Study population and sample

A retrospective cohort of patients will be assembled with patients hospitalized at the postoperative cardiac surgery unit between January 1, 2019, and January 31, 2020. This timeframe will avoid the recruitment of patients during the COVID-19 pandemic, a window of time during which the practice of ACNPs within the unit was inconsistent. Patients will be selected, based on three inclusion criteria: 1) patient admitted with a diagnosis of coronary artery bypass graft (CABG) and/or valve repair, 2) patient age is over 18 years old, and 3) patient has been hospitalized for at least 24 hours in the postoperative cardiac surgery unit. The minimum 24-hour criteria will allow the research team to examine the hospitalization of the patient in the postoperative cardiac surgery unit, which is the setting where ACNPs practice in Québec [35]. Patients will be identified from the electronic databases of the UHC and the diagnostic codes of the Canadian Institute for Health Information [36] (S2 Appendix).

A sample size calculation was conducted in G*power [37]. This project will include 15 variables, including one independent variable, one dependent variable, and 13 confounding variables. The variables selected for this project are described in the next section. To perform one multivariate linear regression model and detect an effect size of *f*^*2*^ = 0.15 with a power of 0.80 and a standard error of 5%, a minimum sample size of 183 patients was estimated.

A total of 300 patients will be selected, based on the sample size calculation and an over-estimation of at least 20%, to consider the risk of error from the presence of missing data and incomplete patient health records [38, 39]. A systematic random selection of 150 patients under the care of interprofessional teams with ACNP will be conducted and matched with 150 patients under the care of interprofessional teams without ACNP. Three criteria [40–43] will be used simultaneously to match each pair (1:1): 1) age (i.e., a five-year gap will be tolerated) 2) sex, and 3) type of cardiac surgery (i.e., CABG, valve repair, or CABG/valve repair).

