Four best-practice guidelines are included in the category of the postoperative assessment performed by interprofessional teams. A daily assessment of the patient’s level of pain, surgical wound(s), nutrition, and mobilization will be measured. For each best-practice guideline recommendation, the achievement of the guideline will be confirmed if at least one postoperative assessment per day is performed by the ACNP or other members of the interprofessional teams during the patient’s hospitalization in the postoperative cardiac surgery unit. The postoperative assessments include the assessment of the clinical manifestations, signs, and symptoms experienced by the patient (e.g., patient’s decrease mobility), as well as the interventions conducted by clinicians following these assessments. Interventions include pharmacological interventions (e.g., prescription of analgesic), non-pharmacological interventions (e.g., prescription of a coronary diet), and clinician consultations (e.g., consultation with the nutritionist). Two additional descriptive variables will be measured for each best-practice guideline, including: 1) the total number of postoperative assessments performed by interprofessional teams during the hospitalization, and 2) the type of associated interventions conducted by clinicians (e.g., non-pharmacological, consultation, etc.).

A composite score will be developed to measure the level of adherence to best-practice guidelines by interprofessional teams with and without ACNPs. A composite score per patient per day of hospitalization in postoperative cardiac surgery will be developed and based on three consecutive steps. Firstly, for each best-practice guideline, a score on a scale of two will be created and points will be attributed for: 1) the achievement of the best-practice guideline recommendation, and 2) the associated intervention performed by clinicians. Points will be given based on the information contained in the patient’s health record and electronic databases. A missed intervention will be considered as a lack of adherence to best-practice guidelines, and no point will be given.

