#### Variables influencing the effect of acute care nurse practitioner practice related to interprofessional teams’ characteristics

Two influencing variables related to interprofessional teams’ characteristics will be measured. First, the cardiac surgeon who performed the surgery and ensured the follow-up of the patient’s recovery will be noted. A confidential code will be created for each surgeon practising in the UHC. Second, a discrete variable will be created to measure the number of consultations conducted by clinicians from different professional groups (e.g., nutrition, rehabilitation team) during the patient’s hospitalization in the postoperative cardiac surgery unit. A categorical descriptive variable will be created to measure each clinician’s professional group, including the following: 1) rehabilitation team (e.g., physical therapist, occupational therapist), 2) respiratory therapist, 3) social worker, 4) skin and wound care therapist, 5) nutritionist, and 6) speciality consultation (e.g., internal medicine, nephrology).

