A multivariate linear regression model will be developed to examine the association between interprofessional teams with and without ACNPs and the level of adherence to best-practice guidelines [63–65]. An examination of the distribution of the data will be performed. In the case of an abnormal distribution of the data, a transformation will be conducted to adjust the statistical model based on the observed data. The independent variables will include the interprofessional teams with and without ACNPs, as well confounding variables. A correlation matrix will be developed, and tolerance value lower than 0.2 and a variance inflation factor (VIF) value higher than 5 will be used to identify multicollinearity between independent variables [63–65]. Independent variables with multicollinearity will be removed one at the time and a new regression will be calculated. The dependent variable of the regression model will be the average composite score (%) of the level of adherence to best-practice guidelines. Statistical significance will be based on a *p*-value of 0.05. Sensitivity analysis will be conducted based on a selection of confounding variables related to the characteristics of the patient (e.g., length of stay, ICU readmission). The selection of these confounding variables will be based on the observed data and descriptive analysis. The residual analysis and the analysis of the R^2^ will be conducted to assess the goodness-of-fit of the multivariate linear regression model.

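### The only model for H1 adjusts for five variables that arise wholly or largely after team assignment, so its ACNP coefficient may not be the effect that H1 asks about

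*Protocol article*

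**What the plan says.** All references are to the Protocol article.

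- **When exposure starts (Study setting).** After the first ICU stay: "Upon admission to the postoperative cardiac surgery unit, patients are assigned to the care of interprofessional teams with or without ACNPs". The basis is organisational: "Team assignment depends on the current workload of each team, and the availability of the beds in the unit".
- **How many covariates (Study population and sample).** "This project will include 15 variables, including one independent variable, one dependent variable, and 13 confounding variables". Variables under study repeats the figure of 13.
- **Which covariates.** The section on patient characteristics lists eleven, including total and unit length of stay, the number of ICU readmissions after the first ICU discharge, and readmission after hospital discharge: "The hospital 30-days readmission at the postoperative cardiac surgery unit after discharge will be measured for each patient from a dichotomous variable". The section on team characteristics lists two, the surgeon and a consultation count for the unit stay: "a discrete variable will be created to measure the number of consultations conducted by clinicians from different professional groups".
- **What enters the model (Data analysis, Objective 3).** "The independent variables will include the interprofessional teams with and without ACNPs, as well confounding variables". The dependent variable is the average composite adherence score. The only rule for dropping a variable is collinearity (tolerance below 0.2, VIF above 5). A sensitivity analysis is planned on a selection of patient variables, with length of stay and ICU readmission as examples, to be chosen from the observed data.
- **What earns points in the score (Dependant variable).** For the four postoperative-assessment guidelines the listed interventions include "non-pharmacological interventions (e.g., prescription of a coronary diet), and clinician consultations (e.g., consultation with the nutritionist").

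**The concern.** A confounder of the comparison between teams must be in place before the team is assigned. A variable that arises afterwards can be affected by the team, by the care being scored, or by unmeasured severity that also affects the score. Holding it fixed then changes the question. The coefficient no longer measures the full difference in adherence between teams. It measures what is left after part of the route may have been blocked, and it may include an association that the adjustment itself induces.

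This regression is the only test of H1. If the team works partly through the adjusted variables, a real effect could be missed. If the adjusted variables share unmeasured causes with adherence, an effect could appear where there is none.

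**Working it through.** **1. Are the five among the 13?** The eleven patient variables are age, sex, total length of stay, surgery type, Charlson index, unit length of stay, 30-day readmission, index ICU hours, prolonged ventilation, failed extubation and ICU readmissions. The two team variables are surgeon and number of consultations. 11 + 2 = 13, and 13 + 1 exposure + 1 outcome = 15. The plan's own counts are reproduced, so none of the five is merely descriptive.

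**2. When is each determined, relative to assignment at unit admission?**

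| Covariate | Timing |
|---|---|
| Unit length of stay | wholly after |
| Total length of stay | first ICU stay before, remainder after |
| ICU readmissions | after the first ICU discharge, so after |
| Consultations in the unit | wholly after |
| 30-day readmission | after discharge, so after the score is complete |
| The other eight | before, provided ventilation and extubation are read from the index ICU stay |

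**3. Does the document give reasons why they could be downstream?**
- Background reports that some studies associate ACNP practice with "reduced length of stay at the hospital after the cardiac surgery". It also lists managing consultations as an ACNP activity.
- Background links higher adherence to fewer complications, and complications to longer stay and more ICU readmission. Stay and ICU readmission could therefore also follow from adherence.
- The criterion-validation section treats 30-day readmission as a performance measure of care.

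**4. How far do consultations overlap the score?** They are named for 4 of 12 guidelines, each with one intervention point, so they touch at most 4/24 = 16.7% of a day's maximum. One consultation that earns one point on one day adds 100/24 = 4.17 percentage points to that day. Assume a unit stay of 8 to 10 days (9 to 11 hospital days less about one ICU day). The patient's average then rises by 4.17/10 to 4.17/8, or 0.42 to 0.52 points, and by nothing if another intervention had already earned the point.

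**5. What can adjustment do?** For least squares with one added covariate M:

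adjusted team coefficient = unadjusted coefficient − (team difference in M) × (slope of the score on M within team).

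The direction depends on the sign of that product. The document gives neither factor, so the values below are assumptions in arbitrary units. The team difference in M is 0.5 throughout. Rejection rates come from simulation (300 patients, 4,000 runs, 5% level).

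| Assumed case | True total effect | Slope on M | Adjusted coefficient | Rejection, unadjusted → adjusted |
|---|---|---|---|---|
| Mediator | 0.35 | 0.30 | 0.35 − 0.5 × 0.30 = 0.20 | 94% → 53% |
| Stronger mediator | 0.35 | 0.50 | 0.35 − 0.5 × 0.50 = 0.10 | 90% → 18% |
| No effect; M and score share unmeasured severity | 0 | −0.20 | 0 + 0.5 × 0.20 = 0.10 | 5% → 17% |

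The first two cases lose effect and the third creates one. None is a forecast for this study.

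**6. Does a smaller set cost patients?** Removing five leaves 13 − 5 = 8 confounders plus team, or 9 predictors if each variable counts once, as the plan counts. Power is taken from the noncentral F distribution with noncentrality 0.15 × N and N − 9 − 1 denominator degrees of freedom. At alpha 0.05 and power 0.80 this needs N = 114 for the whole model, or 55 for the team coefficient alone. The planned 300 exceeds both. The same method with 14 predictors gives 135, not the stated 183; that is a separate matter and nothing here depends on it.

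**The case against.** **The variables stand in for severity.** Long stay and ICU readmission do reflect illness. But the Charlson index, index ICU hours, prolonged ventilation, failed extubation and surgery type already carry severity from before assignment. Assignment by workload and beds also weakens the case for later proxies.

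**The plan has safeguards.** The collinearity rule may well drop one length-of-stay variable, because total stay contains unit stay, so the fitted model may hold fewer than five. It would do so for collinearity and not for timing. The sensitivity analysis names two of the variables, but it is chosen from the data and does not define a model limited to pre-assignment covariates. Both help only in part.

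**The evidence for mediation is mixed.** This stands. Background also reports studies that found no significant association between ACNP practice and patient or organisational outcomes. Mediation through stay would further require stay to affect a per-day average, which the document does not show.

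**Stronger readings are tempting.** A reader might infer any of the following, and the document supports none of them:
- *The ACNP effect will be pulled toward zero by a known amount.* Neither size nor sign can be derived, and the third case above moves away from zero.
- *Consultations are simply part of the outcome.* The overlap is partial. Consultation is one of three kinds of intervention in 4 of 12 guidelines, and the count also covers groups such as social work and respiratory therapy. One consultation scored once moves the average by about half a point at most, under the stay assumed above.
- *30-day readmission can only be a consequence of adherence.* It may instead share causes with adherence. In neither case is it a confounder of team assignment.

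**Fig 1 and the S3 Appendix are not shown.** The text alone accounts for all 13 variables, so the count does not depend on them.

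**Conclusion.** The point holds as a matter of timing. Five of the 13 covariates in the only model for H1 arise wholly or largely after team assignment, total stay only in part, and to that extent cannot confound it. Followed as written, the plan conditions on possible mediators, on a variable that can earn part of the score, and on one observed after the score is complete. No stated rule yields a model free of them.

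The consequence is a coefficient that may understate a real ACNP effect or show one that does not exist. The magnitude is unknown. The illustrative figures rest entirely on assumed path strengths and show only that both directions are possible at 300 patients. The conclusion assumes that the 13 variables listed in the text are those meant by the confounding variables in Objective 3; the matching counts support this.

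**What to change.** State in Objective 3 that the main model adjusts only for variables fixed before unit admission: age, sex, surgery type, Charlson index, index ICU hours, prolonged ventilation and failed extubation in the index ICU stay, and surgeon. Specify that the ventilation and extubation variables refer to the index ICU stay.

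Report unit and total length of stay, ICU readmissions, consultations and 30-day readmission descriptively or as secondary outcomes. If a model containing any of them is wanted, specify it in advance and label it as a sensitivity analysis that does not estimate the total team effect. Amend the count of confounding variables wherever it appears.

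The cost is a change of wording. No new data are needed, and 300 patients remain enough for the smaller model on the plan's own effect size. The downside is that slightly less residual variance is explained. A mixed model on the daily scores would be one way to handle unequal stays, but it is optional and not part of the required change.

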#### Variables influencing the effect of acute care nurse practitioner practice related to interprofessional teams’ characteristics

Two influencing variables related to interprofessional teams’ characteristics will be measured. First, the cardiac surgeon who performed the surgery and ensured the follow-up of the patient’s recovery will be noted. A confidential code will be created for each surgeon practising in the UHC. Second, a discrete variable will be created to measure the number of consultations conducted by clinicians from different professional groups (e.g., nutrition, rehabilitation team) during the patient’s hospitalization in the postoperative cardiac surgery unit. A categorical descriptive variable will be created to measure each clinician’s professional group, including the following: 1) rehabilitation team (e.g., physical therapist, occupational therapist), 2) respiratory therapist, 3) social worker, 4) skin and wound care therapist, 5) nutritionist, and 6) speciality consultation (e.g., internal medicine, nephrology).

### Data collection

An extraction tool will be developed and pilot-tested, based on the best-practice guidelines and the confounding variables related to the patient and interprofessional team characteristics (Fig 1). One extraction will be completed per patient per day during the hospitalization in the postoperative cardiac surgery unit, by the first author or a research assistant. The development of the extraction tool followed the Consensus-based Standards for the selection of health measurement instrument (COSMIN) guidelines [46] and will include three stages: the content validation; the criterion validation; and the pilot-test.

